## Methods

### Study Design and Setting

This 12-month prospective observational cohort study will recruit 200 families at the Asthma Clinic of the Centre Hospitalier Universitaire Sainte-Justine, a tertiary care pediatric hospital in Montreal, Canada. The asthma clinic has a routine standardized collection of patient demographics (age and sex), disease (phenotype, control, and triggers), and treatment (dose, format, and frequency) characteristics. With patients’ consent, clinical data can be linked with the *Registre de données sur les Medicaments* (reMed) database [63], which collects all data on medication dispensed by all pharmacies in the province of Québec.

### Ethics Approval

The study was reviewed and approved by the Institutional Review Board of the Centre Hospitalier Universitaire Sainte-Justine Research Centre (protocol no: 2022-3888) and has been registered (ClinicalTrials.gov ID: NCT05278000).

### Participants

Parents of children aged 2-17 years seen at the clinic with a diagnosis of asthma, made according to Canadian national guidelines [64], will be eligible for the study. This age range will help us explore whether the relationships identified vary by the age group of the child (preschool vs school-age vs adolescents).

The inclusion criteria will include (1) children with documented prescription for a controller medication at recruitment visit including at least one of the following: inhaled corticosteroids, long-acting beta-agonists, or leukotriene receptor antagonists and (2) consent to access the reMed database (see section *Study Design and Setting* above).

Participants will be excluded if (1) their child has another chronic pulmonary disease (eg, cystic fibrosis) and (2) parents have insufficient knowledge of French or English to complete the questionnaires.

Potential participants will be identified by a research assistant through prescreening of clinical patient lists. Specifically, the research assistant will prescreen patient lists for the following month and will confirm patient lists using physicians’ daily appointment roster upon arrival at the clinic on each day of recruitment.

### Recruitment

We will recruit 200 families, stratified to recruit 40 families geographically from each quintile of the Pampalon material deprivation index [65-67]. Refer to the *Power Calculation and Feasibility* section for the method of determining the sample size. The Pampalon material deprivation index, measured at the level of the dissemination area and associated with the postal code of the child’s primary residence, is a composite of the (1) proportion of persons without a high school diploma, (2) employment:population ratio, and (3) average personal income obtained from the Canadian census [65,66].

Previous evidence suggests that adherence decreases with the age of the child, coinciding with responsibility for taking medication shifting from parents to their children as they age [53-59], whereas evidence for the impact of children’s sex is mixed [56,57,62,68,69]. We will stratify our recruitment to ensure equal recruitment between age groups (2-7, 8-12, and 13-17 years), and all analyses will consider the child’s age and sex [4].

### Consent

Informed consent will be obtained from all participants in the asthma clinic, before enrollment, including consent for follow-up measures and access to clinical data in the reMed database. Consent forms and questionnaires will be administered in French and English according to each participant’s preference.

Participants will be approached by a trained research assistant at the time of their clinic appointment. Given the patient flow and clinic organization, participants may be approached in the waiting room before their appointment, between parts of their appointment (ie, after seeing the nurse and before seeing their physician), or after having completed their appointment. The research assistant will approach the patients and describe the project and what their participation would require. Those who express interest in participating will accompany the research assistant to a private room where they will be given the opportunity to read the project consent form, with the research assistant available as needed to explain further or respond to questions. Participants who agree to participate will be asked to sign and date the consent form (either on paper or electronically using the REDCap [Research Electronic Data Capture; Vanderbilt University] database where the survey is hosted) as well as complete the consent form and questionnaire for inclusion in the reMed database, which is required for study participation (given that adherence to medication, obtained from this database, is the primary outcome). Participants will then complete the questionnaire on the REDCap database with guidance from the research assistant throughout.

### Follow-up

Participants will be followed prospectively for 12 months after recruitment with measurements at baseline, 6 months, and 12 months (Figure 1). Using the REDCap database, they will be sent the follow-up questionnaires immediately following the baseline questionnaire and at the 6- and 12-month follow-ups. Refer to Figure 1 for the details of each measure.

**Figure 1 figure1:**
[figure not shown]
Data collection and schedule of events. REDCap: Research Electronic Data Capture.

### Outcome Measures

Details of each measure, including operational definitions and data collection methods, are described in the following sections (*Primary Outcome*, *Main Predictors*, *Other Measures and Covariates*, and *Follow-up Measures* sections) and detailed in Table 1.

**Table 1 table1:** Overview of measures, data sources, and timeline of measures.

Measure		Measurement details	Data source	Timeline		
				Recruitment	6-month follow-up	12-month follow-up
**Primary outcome**						
	*Adherence*^a^*:* Proportion of prescribed days covered	Number of days for which the drug was dispensed by a pharmacy divided by the number of days for which it was prescribed [63,70]	Pharmacy claims data (*Registre de données sur les Médicaments*)	—^b^	—	X^c^
**Main independent variables**						
	*Unmet social needs*	A series of validated questions assessing employment [71], housing stability and ability to pay for utilities, [72-75], financial resource strain [76-78], food security [79], transportation [75], childcare [80], and parent education and health literacy [80,81]	Questionnaire	X	X	X
	*Scarcity, via executive control—*Eriksen flanker task	Speed of response and percentage accuracy [82-84], Δ accuracy between easy and hard condition	In-person computer-based task	X	X	X
	*Future discounting—*Kirby delay discounting task	27-item questionnaire assessing temporal discounting	Questionnaire	X	X	X
**Exploratory measures**						
	*Capability*	Perceived Competence Scale [85,86]	Questionnaire	X	—	—
	*Motivation*	Treatment Self-Regulation Scale (adapted for adherence) [87]	Questionnaire	X	—	—
	*Perceived stress:* perceived stress scale	4-item measure used to understand how respondents perceive stress and how their feelings are impacted by certain situations [88]	Questionnaire	X	X	X
	*Asthma severity*: PPACI^d^	4-level PPACI assessed in the preceding 6-month period. On the basis of the number of doses per week of short-acting beta-agonists, use of oral corticosteroids within 14 days of a medical claim or hospitalization for asthma, any ED visit for asthma, and any hospitalization for asthma [89]	Medical chart	X	X	X
	*Access to resources*	Whether families accessed resources to which they were referred (social worker at local community health center)	Questionnaire	—	X	X
	*Asthma treatment satisfaction*	Single item inquiring who is primarily responsible for the child’s asthma management and 1 question drawn from the Asthma Medication questionnaire [90] adapted to inquire specifically about management of one’s child’s asthma	Questionnaire	X	X	X
	*Asthma responsibility questionnaire*	10-item measure examining the division of asthma management responsibilities between child and parent [91]	Questionnaire	X	—	X
**Covariates**						
	Child’s *age* and *sex*	N/A^e^	Medical chart	X	—	—
	Child’s *gender*	N/A	Questionnaire	X		
	*Caregiver’s relationship with child*	Two items interrogating relationship to the child and whether respondent is the child’s legal guardian	Questionnaire	X	—	—
	*Caregiver’s gender*	N/A	Questionnaire	X	—	—
	*Caregiver’s marital status* and *living situation*	Single items assessing marital status and living situation as it relates to the child	Questionnaire	X	—	—
	*Postal code of the child’s residence*	N/A	Questionnaire	X	—	—
	*Caregiver’s level of education*	Elementary school or less, some high school, high school graduate, some college or technical school, college graduate, or completed a graduate degree	Questionnaire	X	—	—
	*Household income*	One item question based on the Canadian income survey [92]	Questionnaire	X	—	—
	*Presence of a smoker or e-cigarette user in the house*	2 question items investigating use of tobacco products or e-cigarettes in the last month [93]	Questionnaire	X	X	X
	*Responsibility for asthma management*	“Who is responsible for asthma management?”	Questionnaire	X	—	—
	*Child’s ethnicity, immigration status*, and *language spoken at home*	Questions using categories from Canadian census [94]	Questionnaire	X	—	—
	*Class of controller medication received during study period*	Inhaled corticosteroids and long-acting beta-agonists of leukotriene receptor antagonists	Medical chart	X	X	X

^a^The name of the variable in question has been italicized.

^b^Em dashes in the timeline signify that data for the associated variable will not be collected at the time point in question.

^c^X in the timeline indicate data collection for the associated variable at the time point (recruitment, 6-month follow-up, or 12-month follow-up) in question.

^d^PPACI: Pediatric Pharmacoepidemiology Asthma Control Index.

^e^N/A: not applicable.

### Primary Outcome

*Adherence to controller medication* will be measured for the 12 months of follow-up on a scale of 0%-100% by the *proportion of prescribed days covered (PPDC)*, a validated index calculated as the number of days for which the drug was dispensed by a pharmacy divided by the number of days for which it was prescribed [63]. The PPDC accounts for varying durations of physician prescriptions [70] and leads to conservative estimates of adherence, as possession of medication is a prerequisite for adherence but does not confirm its use. The PPDC will be calculated using medical records (prescriptions made by the clinician) and the reMed database [24,63]. reMed collects drug claims for both privately and publicly insured children.

### Main Predictors

*Scarcity* is a state in which individuals’ cognitive resources (mental bandwidth) are occupied and taxed by preoccupations, including pressing financial concerns [31]. These worries consume mental bandwidth, leaving less of it available for other tasks. In this study, we will assess scarcity as per the original work in the field [95]. Briefly, participants will be exposed to hypothetical scenarios that are designed to elicit a scarcity mindset in those who are experiencing a state of scarcity. The scenarios bring to the fore participants’ scarcity mindset by asking participants to imagine themselves in situations in which they would need to access scarce resources. Specifically, participants will be asked to imagine requiring an urgent car repair, costing either US $1500 in the more taxing, “hard” scenario or US $150 in the “easy” scenario. Similarly, participants will be asked to imagine that their child required either a hospitalization (hard scenario) or an ED visit (easy scenario) for their asthma. After listening to the scenarios, participants will complete the Eriksen flanker task, a widely used, standardized, and validated test of executive function assessing selective attention, information processing, and inhibitory function. The task requires participants to rapidly identify whether a series of arrows, colored boxes, or letters are congruent or incongruent (Figure 2). We will measure both the percentage accuracy and time to complete the task under each condition [31,82,95]. The outcome for each participant will be the difference in accuracy on the flanker test after the easy versus the hard scenarios.

**Figure 2 figure2:**

Flanker task with arrows, illustrating congruent and incongruent series of arrows.

*Future discounting* will be assessed using Kirby delay discounting task, in which participants are asked to choose between a smaller, immediate financial reward or a larger, delayed reward. From the participant’s answers to the 27 choices, a hyperbolic discount parameter (k) is calculated [96].

*Unmet social needs* will be assessed using validated measures of employment [71], housing stability, ability to pay for utilities [72-75], financial resource strain [76-78], food security [79], transportation [75], childcare [80], parent education, and health literacy [80,81]. We chose these needs as they had published and validated short question items assessing them, had either documented or plausible relationships with asthma, and could be amenable to intervention by social workers.

Families for whom unmet social needs have been identified will be asked whether they are interested in receiving support to address their needs. If they are interested, the study team will ensure referral to a social worker at a *centre locaux de services communautaires* (local community services centers), a service covered by the government’s universal health insurance plan. With the participants’ consent, their treating clinician will be informed of their unmet social needs and whether they were referred to a local community services center. Participants who agree to be referred to resources to address their unmet social needs at recruitment will be asked at 6 and 12 months if they accessed any resources to help them address their unmet needs and, if so, which ones. In our analysis, among participants with identified unmet social needs, we will explore whether the participants’ desire for a referral for social services and, if applicable, access to those resources influenced the relationship between unmet social needs and adherence.

### Other Measures and Covariates

*Family and sociodemographic characteristics* will include the child’s age, sex, gender, ethnicity, and immigration status and parent participants’ gender, race and ethnicity, level of education, and income. We will also inquire about the presence of a smoker in the household and the languages spoken at home.

*Asthma and asthma treatment information* will include controller medication type (inhaled corticosteroids, long-acting beta-agonists, or leukotriene receptor antagonists) and frequency (once vs twice daily) retrieved from medical records and asthma disease severity in the 6 months preceding recruitment using the 4-level Pediatric Pharmacoepidemiology Asthma Control Index (PPACI) using data from medical records. The PPACI categorizes asthma control based on the average number of doses per week of short-acting beta-agonists, any use of oral corticosteroids within 14 days of a medical claim or ED visit for asthma, and any hospitalization for asthma [89].

*Perceived efficacy of medication* will be assessed using a single item on a 5-point scale selected from the Patient Satisfaction with Asthma Medication questionnaire: “Would you recommend your child’s asthma medication and its inhaler to someone else with asthma?” [90].

*Perceived stress of respondents* will be measured using the 4-item version of the Perceived Stress Scale, with each question rated on a 5-point scale [88,97]. The 4-item Perceived Stress Scale has a Cronbach α reliability coefficient of .72.

*Capability and Motivation* will be measured using a questionnaire based on the Capability, Opportunity, Motivation, and Behavior model [98]. This will serve to evaluate the mechanism by which scarcity and future discounting may influence medication adherence.

*Capability* will be measured using the 4-point Perceived Competence Scale, validated in adherence to medication as well as in the pediatric population [85,86]. These 4 items inquire specifically about the parent’s perceived confidence and capability in ensuring that their child takes their asthma medication as prescribed.

*Motivation* will be assessed using selected items from the 15-item Treatment Self-Regulation Scale adapted for adherence [87]. The 2 selected items assess the perceived importance that their child takes their asthma medication as prescribed and their confidence in ensuring that they do so. Selected items, rather than the full scale, were chosen to limit participant burden.

*Division of asthma treatment responsibility* will be assessed using the 10-item Asthma Responsibility Questionnaire, which measures the division of asthma management responsibilities between child and parent [91]. It also measures the parent’s degree of satisfaction with the amount of responsibility their child takes for their asthma.

### Follow-up Measures

At 6 and 12 months, we will assess health service use, specifically asthma-related ED visits and hospitalizations, via parental reports as well as the patient’s hospital file and provincial health insurance data. We will also measure access to resources to address unmet social needs for participants who agreed to be referred to a social worker at their local community services center using a single-item question for each identified unmet social need (eg, “Since you entered this study, have you been in contact with a social worker or someone from the local community services centre to help you access resources for [identified unmet social needs]?”)

### Study Procedures

Families will be made aware of the project via a posting in the clinic’s regular electronic newsletter and posters in the clinic waiting room. Clinicians will be informed about the study through personalized emails from the study team. A research assistant will be present during each clinic day, prescreen clinic lists for eligible families, and approach primary caregivers for consent at the time of their clinic visit.

### Study Assessments

The study flow, including the measurements at each time point, is shown in Figure 1. Measures will be completed on the web via the REDCap platform [99], except for the flanker task, which will be administered via the testable web-based platform.

### Baseline

Potential participants will be approached by the research assistant during clinic hours, before their child’s appointment with their treating physician. After ensuring that participants are eligible based on the inclusion and exclusion criteria, participants who consent to the study will be randomized to 1 of 4 groups, which determines the order in which they will complete the baseline questionnaire, the flanker task while primed with easy scenarios, and the flanker task while primed with hard scenarios. Details of the questionnaire sequences and randomization groups are shown in Figure 1. The participants will complete the baseline questionnaire on site guided by the research assistant. This includes the following measures (detailed in the *Primary Outcome*, *Main Predictors*, *Other Measures and Covariates*, and *Follow-up Measures* sections above): (1) scarcity assessment (flanker task)—2 rounds, once while primed with “hard” scenarios and once while primed with “easy” scenarios; (2) family and sociodemographic characteristics; (3) unmet social needs; (4) identification of person primarily responsible for the management of the child’s asthma and satisfaction with asthma treatment; (5) Perceived Stress Scale; and (6) Kirby delay discounting task to assess future discounting.

To ascertain whether exposure to the scarcity-inducing scenarios and the subsequent completion of the flanker task impact self-reporting of unmet social needs, participants will be randomized to complete the flanker task either before or after having completed the other sections of the questionnaire. Similarly, to determine whether familiarity with the flanker test influences accuracy and speed rather than the type of scenario (easy vs hard), participants will be randomized to start with either the easy or the hard scenarios. A visual representation of the 4 permutations is presented in Figure 1.

### Secondary Questionnaire

Immediately after the recruitment visit, participants will be emailed a secure link for a secondary questionnaire including (1) the Asthma Responsibility Questionnaire [91] and (2) questions drawn from the Perceived Competence Scale [85,86] and the Treatment Self-Regulation Scale (adapted for asthma treatment adherence) [87]. This division of the baseline and secondary questionnaire was chosen to limit participant burden and time required at the clinic on the day of recruitment.

### Follow-up Questionnaires

Participants will be emailed 6 and 12 months after recruitment to complete the follow-up questionnaires, the contents of which are described in Table 1. Participants will be reminded and offered help to complete the questionnaire if not completed within a week via up to 2 email reminders and 1 phone call from the research assistant.

### Participant Compensation

Participants will receive CAD $10 (US $7.50) in compensation for completion of the initial study questionnaire and CAD $10 (US $7.50) at the end of the study if all materials have been completed.

### Statistical Analysis

Results will be reported following the recommendations of the Strengthening the Reporting of Observational Studies in Epidemiology Statement for cohort studies [100]. For *aim 1*, we will first perform descriptive statistics for our measures of executive function (accuracy and time to complete the Eriksen flanker task between easy and hard scenarios) at baseline, 6 months, and 12 months and model trajectories using mixed effects regression models. We will then quantify the relationship between both level of scarcity at baseline and trajectories with PPDC in the 12 months following the index visit. We will use unadjusted linear regression models, before adjusting for potential confounders, including sociodemographic factors (eg, child age and sex) and disease characteristics (eg, PPACI at baseline and class and dosing frequency of controller medication). We will perform collinearity diagnostics on potential confounders, and if significant correlation is identified, we will adjust our model accordingly. Exploratory analyses will use logistic and ordinal regression models and the same set of variables to examine any effect of scarcity on health service use (ED visit or hospitalization). We will use the same analysis plan to examine the relationship between future discounting (using Kirby’s discount parameter) and PPDC.

For *aim 2*, we will first assess whether scarcity and future discounting scores at baseline differ between families with versus those without unmet social needs. In the subgroup with identified unmet social needs at any time during the study, we will use regression models with time-varying exposure to estimate the effect of referral to social services and access to services on the presence of unmet social needs (ie, determine if referral to social services led to improvement in unmet social needs). We will then use generalized estimating equations to estimate the effect of unmet social needs on cognitive capacity, executive control, and future discounting.

For *aim 3*, we will evaluate whether scarcity is a mediator of the relationship between unmet social needs and adherence with multiple regression models using a recognized approach [101]. We will use a similar analysis for future discounting.

For *aim 4*, we will use multivariable logistic regression models to examine the effect of unmet social needs on ED visits (any vs none) and hospitalizations (any vs none), testing whether there is an interaction between medication adherence and unmet social needs in this relationship (whether better adherence is protective in children with unmet social needs). A similar approach will be used for asthma control using an ordinal regression model for the 4-point PPACI.

For *aim 5*, we will use descriptive statistics to document the prevalence of unmet social needs in our sample as well as within families and use logistic regression models to test whether referrals to social services modulate those trajectories.

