**Methods:**

This 12-month prospective observational cohort study will recruit 200 families of children aged 2 to 17 years at the Asthma Clinic of the Centre Hospitalier Universitaire Sainte-Justine, a tertiary care pediatric hospital in Montreal, Canada. The primary outcome will be adherence to controller medication, measured using the proportion of prescribed days covered during follow-up. Exploratory outcomes will include health care use. The main independent variables will be unmet social needs, scarcity, and future discounting, measured using validated instruments. These variables will be measured at recruitment as well as at 6- and 12-month follow-ups. Covariates will include sociodemographics, disease and treatment characteristics, and parental stress. Primary analysis will compare adherence to controller medication, measured using the proportion of prescribed days covered, between families with versus those without unmet social needs during the study period using multivariate linear regression.

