### Power Calculation and Feasibility

Previously published data using the asthma clinic database found a mean PPDC (our measure of adherence and primary outcome) of 68%, with an SD of 33% [24]. In previous studies, a 25% [102] or 1 SD difference [103] in adherence was associated with significant differences in the number of ED visits. As those studies used slightly different measures of adherence, we will be conservative and power our study to detect a 16% difference (half an SD) in PPDC between the participants above and below the median of scarcity and future discounting scores. Using 2-sample *t* tests (2-tailed), an α of .05, and a power of 0.8, this will require us to recruit 135 participants. Accounting for 30.4% (41/135) of missing data (covariates) and loss to follow-up, we will recruit 200 participants. The prevalence of unmet social needs in the clinical population is unavailable; however, in our patient population, 26.59% (335/1260) of children are from the lower quintile of the material deprivation index. In addition, recent Canadian data suggest a food insecurity prevalence of 29% among youth and young adults [104]. Assuming that 25% (50/200) of participants have at least one unmet social need, the proposed sample size will allow 85% power to detect a 16% difference (half an SD) in adherence between those with versus without unmet social needs.

On the basis of preliminary data from the asthma clinic, 87.68% (1139/1299) of patients who were prescribed daily controller medications consented to reMed. In another study ([name] et al, unpublished data, August 2023) from our clinic with a similar population and participant burden, 30% of eligible families consented to participate in the study. Using this ratio, we would need to approach approximately 670 families to obtain our desired sample size. There are at least three half-day clinics a week where recruitment could occur, with a minimum of 3 families per clinic. Using a conservative estimate, even if 29.9% (200/670) of families consent to participate, recruiting 200 participants will take 18 months.

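### Aim 2 estimates the effect of referral on unmet needs in a subgroup partly selected on that outcome, so an ineffective referral can give an odds ratio well away from 1, in either direction

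*Protocol article*

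**What the plan says.** For aim 2, the Statistical Analysis section of the Protocol article defines the population and exposure as: "In the subgroup with identified unmet social needs at any time during the study, we will use regression models with time-varying exposure". The purpose is "to estimate the effect of referral to social services and access to services on the presence of unmet social needs", which the text explains as an attempt to "determine if referral to social services led to improvement in unmet social needs".

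Needs are assessed at three visits; the Abstract says of the main independent variables: "These variables will be measured at recruitment as well as at 6- and 12-month follow-ups".

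Referral depends on having a need. Under Main Predictors: "Families for whom unmet social needs have been identified will be asked whether they are interested in receiving support to address their needs". Later access to services is tracked for a defined group: "Participants who agree to be referred to resources to address their unmet social needs at recruitment will be asked at 6 and 12 months". No section clearly describes a fresh referral offer at 6 months.

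The only prevalence figure is in Power Calculation and Feasibility: "Assuming that 25% (50/200) of participants have at least one unmet social need". The document gives no rate for needs resolving, for new needs arising or for referral uptake.

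**The concern.** Entry to the subgroup depends on the outcome, including outcomes measured after baseline. A family with a need at recruitment is included whatever happens later. A family without one is included only if its own later outcome turns positive.

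These late-need families could not have been referred before the need appeared. They supply an unreferred, need-present visit by construction. If the need first appears at 12 months, they also supply an unreferred, need-absent visit at 6 months. Coding referral as time-varying classifies exposure correctly at each visit but does not undo the selection into the subgroup.

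What is at stake is a causal statement about referral. A protective, null or harmful estimate could each arise from the selection alone.

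**Working it through.** **Inputs.** From the document: 200 families, 25% (50) with a need at baseline, visits at 0, 6 and 12 months. Assumed, because the document gives no figures: probability *p* that a need persists over 6 months, probability *i* that a new need arises over 6 months, and referral uptake *u*, unrelated to prognosis. Referral has no effect in any calculation.

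**The plan's own figure.** No figure is stated for the referral analysis. The one calculation that uses the 25% prevalence is the power for adherence. With 50 versus 150 families, a difference of 16 and an SD of 33, the standard error is 33 × √(1/50 + 1/150) = 5.39 and 16/5.39 = 2.97. Power is Φ(2.97 − 1.96) ≈ 84%, against the stated 85%. It reproduces.

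**Worked case: *p* = 0.5, *i* = 0.10, *u* = 0.8, referral at recruitment only.**

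- Need at baseline: 50 families, of whom 40 are referred and 10 are not. Need at 6 months is 50%. At 12 months it is 0.5 × 0.5 + 0.5 × 0.1 = 30%.
- No need at baseline: 150 families. New need at 6 months: 15. New need at 12 months among the other 135: 13.5. So 28.5 families enter late.
- Subgroup size: 50 + 28.5 = 78.5, of which 28.5/78.5 = 36% enter through a later outcome.

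| | Need at 6 months | Need at 12 months | Pooled visits with need / without |
|---|---|---|---|
| Referred (40) | 20 | 12 | 32 / 48 |
| Unreferred, baseline need (10) | 5 | 3 | 8 / 12 |
| Unreferred, late need (28.5) | 15 | 15 × 0.5 + 13.5 = 21 | 36 / 21 |
| All unreferred (38.5) | 20 | 24 | 44 / 33 |

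Pooled OR = (32/48)/(44/33) = 0.667/1.333 = **0.50**. At 12 months alone, need is 12/40 = 30% versus 24/38.5 = 62%, OR (12/28)/(24/14.5) = 0.26. The true OR is 1.

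**Same case with *p* = 0.9.**

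- Referred: 36 with need at 6 months; 36 × 0.9 + 4 × 0.1 = 32.8 at 12 months. Pooled 68.8 / 11.2.
- Unreferred: 9 + 15 = 24 at 6 months; 8.2 + 13.5 + 13.5 = 35.2 at 12 months. Pooled 59.2 / 17.8.
- Pooled OR = (68.8/11.2)/(59.2/17.8) = 6.14/3.33 = **1.85**.

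The sign flips because most referred families keep their need, while the 13.5 families whose need arises at 12 months each add an unreferred, need-free visit at 6 months.

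**Range.** Exact enumeration over *i* = 5-15% and *u* = 50-80%, with later needs either referred or not, pooled over 6 and 12 months:

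| Persistence *p* | OR under no effect |
|---|---|
| 0.5 | 0.47-0.76 |
| 0.7 | 0.78-1.02 |
| 0.8 | 1.04-1.32 |
| 0.9 | 1.40-2.60 |

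Late-need families make up 23-45% of the subgroup across this grid. On a wider grid (*p* 0.4-0.9, *i* 5-20%, *u* 30-80%), adjusting for need at the previous visit within the same subgroup does not help: OR 0.29-0.79.

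**Check of the remedy.** Keep only intervals that start with a need, in the worked case with *p* = 0.5:

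- 0 to 6 months: referred 20/40, unreferred 5/10; both 50%.
- 6 to 12 months: referred 10/20; unreferred 10/20 (5 with a baseline need and 15 new at 6 months); both 50%.

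The OR is 1.00, and it is 1.00 in every scenario of the range above.

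**The case against.** The strongest reply is that the phrase only describes who is eligible, with follow-up starting once a need is identified. Improvement can only be judged from a visit at which a need exists, and an article may leave the risk set to the analysis plan. This reading is possible, but the sentence does not state it. The population, outcome, exposure coding and causal reading are all written down, and the population is defined over the whole study. Even if only visits after the first identified need are used, the null OR is 0.83-1.20: much closer to 1, but not 1.

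Three stronger readings should be set aside.

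- A reader might infer that the bias always favours referral. It does not: the pooled OR exceeds 1 at 80-90% persistence. Several of the listed needs (education, health literacy, employment, housing) could plausibly be that persistent.
- A reader might infer that referred families can only stay the same or improve. That fails after 6 months, since a resolved need can recur by 12 months.
- A reader might infer that aim 5, which will "use logistic regression models to test whether referrals to social services modulate those trajectories", has the same bias. Its text names no ever-need subgroup, so this does not follow.

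It also stands that the effect of referral is not among the three primary relationships or the two exploratory aims under Scientific Objectives. The Discussion places an intervention and a randomized trial at a later stage.

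**Conclusion.** The concern holds in this limited form. The aim 2 referral analysis conditions partly on its own outcome, and no other section corrects this. Under a null referral the OR can be about 0.5, about 1 or above 2, depending on persistence, incidence of new needs and uptake. Only the 25% baseline need comes from the document, and that is itself an assumption there, so the figures are illustrations and not predictions. The roughly halved figure is an odds ratio at moderate persistence and high uptake; it is not a general result. What does not depend on the assumed rates is that late-need families enter through their own outcome, so the estimate cannot be read as benefit, harm or absence of effect. This is a secondary sub-analysis and should be corrected before analysis. The primary adherence comparison is not affected.

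**What to change.** For aim 2:

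- Restrict the analysis to family-intervals that start with a need: need at baseline for status at 6 months, and need at 6 months for status at 12 months.
- Compare by referral or access status known at the start of, or during, that interval. State whether a new referral offer is made at 6 months; if not, use the recruitment referral only.
- Adjust for the number and type of needs at the start of the interval, with generalized estimating equations for repeated intervals from one family.
- Replace the causal wording about improvement with wording about association. Families choose referral, and the restriction removes the outcome-based selection but not that self-selection.

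The cost is a change of wording, using needs and access data already planned. The downside is that fewer family-intervals contribute, so the estimate will be less precise.
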